### **Definition of Adverse Events for the trial**

In all cases AEs and / or laboratory abnormalities that are critical to the safety evaluation of the participant must be reported to the Sponsor; these may be volunteered by the participant, discovered by the investigator questioning or detected through physical examination, laboratory test or other investigation.

All SAEs/SARs/SUSARS must be reported to the Sponsor

### **Expected Serious Adverse Events for the trial**

Any expected SAEs for the disease and trial drug / intervention?

### **Adverse events that do not require reporting**

Normal menstrual bleeding, including vaginal spotting, will not be classed as an adverse event and therefore does not need reporting. It will be recorded in the participants' family history notes as part of the study visit information.

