### 5.6.3 Pregnancy/genital bleeding

Participants who become pregnant or, develop genital bleeding of unknown aetiology or for reasons other than uterine fibroids on the study must discontinue ulipristal acetate immediately. Note; partial or complete cessation of menstruation is an expected effect of UA therapy. Delayed menstruation and intermittent vaginal bleeding/spotting are expected effects and do not require cessation of therapy.

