### **Visit 1 Day 29 + 4 / - 7 days (week 5)**

During this visit the participant will:

- be asked if they are happy to continue in the trial and the importance of using contraception throughout the trial will be emphasised.
- have changes in concomitant medications documented
- have a urine pregnancy test performed
- have blood samples taken for LFT of which bilirubin, ALT, ALP, LDH will be measured. If ALT is more than three times the upper limit of normal, UA must be permanently discontinued.
- have their weight recorded
- have any adverse events documented and be asked whether they have had any vaginal bleeding.
- have a drug accountability check performed

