### 8.4.2 Secondary endpoints

Secondary endpoints are the change in the relevant outcome with UA therapy across the whole population of participants:

- Percentage of luminal, basal and mixed colonies by morphological analysis of adherent feeder layer assay
- Percentage of luminal progenitor cells (EPCAM+/CD49f+) by FACS analysis
- Tissue stiffness assessed as the reduced indentation modulus by atomic force microscopy
- Mean tissue section percentage fibrillar collagen assessed by picrosirius red staining and polarised light microscopy
- Background parenchymal enhancement assessed by magnetic resonance imaging (MRI)
- The side effect profile of UA in this patient population assessed by CTCAE v4.03

- The relative change in Ki67 with UA treatment between those with and without known mutation in BRCA1/2 genes

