### 13.1 Recording and reporting of SAEs AND SUSARs

**MFT SOP Pharmacovigilance for Trust-Sponsored Clinical Trials of Investigational Medicinal Products (CTIMPs) must be used for safety reporting.**

AEs, ARs, SAEs, SARs and SUSARs must be recorded and reported as follows:

- For AEs / SAEs – from consent until the time of the last participant visit
- For ARs / SARs and SUSARs – from the 1st IMP dose until the time of the last participant visit

All AEs must be recorded in the participant's CRF in the AE log and in the patient's family history notes. SAEs/SARs/SUSARs must be recorded in the participant's CRF in the AE log and in the patient's family history medical records and must be reported to the Sponsor and other relevant departments/individuals **within 24 hours** of the research staff becoming aware of the event according to the instructions in **SOP Pharmacovigilance for Trust-Sponsored Clinical Trials of Investigational Medicinal Products (CTIMPs) must be used for safety reporting.**

(S)AEs and (S)ARs will be evaluated for duration and intensity according to National Cancer Institute Common Terminology Criteria for Adverse Events V4.0 (NCI-CTCAE) or MedDRA (Medical Dictionary for Regulatory Activities)

Investigator reports of suspected SARs will also be reported by the CI or their delegate to Gedeon Richter (manufacturer).

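### On-treatment vaginal spotting, an effect the protocol expects from UA, has no specified route into the CTCAE side effect endpoint

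*Protocol*

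**What the plan says.** Four parts of the protocol bear on the point.

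- **Section 13, on events exempt from reporting:** the rule reads "Normal menstrual bleeding, including vaginal spotting, will not be classed as an adverse event and therefore does not need reporting". On where it goes instead: "It will be recorded in the participants' family history notes as part of the study visit information".
- **Section 5.6.3:** straight after describing loss of menstruation as something to expect from UA, it continues: "Delayed menstruation and intermittent vaginal bleeding/spotting are expected effects and do not require cessation of therapy".
- **Section 8.4.2:** the secondary endpoints include "The side effect profile of UA in this patient population assessed by CTCAE v4.03".
- **Section 13.1:** "All AEs must be recorded in the participant's CRF in the AE log and in the patient's family history notes". The same section has adverse events and adverse reactions, serious or not, evaluated by CTCAE or MedDRA.

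Section 7.1 provides for the question to be put to the women. At visit 1 the participant will "have any adverse events documented and be asked whether they have had any vaginal bleeding", and the same item appears at visit 2, visit 3 and the VAB 2/prophylactic mastectomy visit.

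**The concern.** A side effect profile should contain the effects that the investigators expect the drug to have. Here one section expects spotting on UA, and another takes spotting out of the class of events for which logging and grading are laid down. If staff follow both, the endpoint is compiled without a bleeding effect that the protocol itself foresees.

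Tolerability is central to the case for this drug. Section 1.1 attributes the low uptake of existing preventive agents partly to their toxicity and presents UA as well tolerated. The participants are women at increased risk without a history of breast cancer, for whom bleeding disturbance is a relevant burden. A profile that understates it would give later prevention trials a flattering starting point.

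**Working it through.** No arithmetic applies: the protocol gives neither a spotting rate nor a target figure for the side effect endpoint. The check is to follow one event through the text, namely intermenstrual spotting in a woman taking UA.

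1. **Is it an effect of the drug?** Section 5.6.3 places intermittent bleeding/spotting among the expected effects, in a note about UA therapy. It would usually also be a change from entry, since section 6.1 requires regular menses (within 3 days of the expected date) and section 6.2 excludes genital bleeding of unknown aetiology.
2. **Is it an adverse event?** The general definition in section 13 covers any untoward occurrence, whether or not the product caused it, so being expected does not by itself remove an event. Expectedness is assessed separately, against the reference safety information. The exemption goes further than waiving a report to the sponsor: it withdraws adverse event status from normal menstrual bleeding and includes spotting in that phrase. It does not say whether spotting outside a period is meant, and section 5.6.3 uses the same word for the drug effect.
3. **Where is it recorded?** The exemption names the family history notes. Section 13.1 requires entry in the CRF adverse event log for adverse events, which the exempted event is not.
4. **Is it graded?** Section 13.1 prescribes CTCAE evaluation for adverse events and reactions. No section prescribes it for exempted bleeding.
5. **Does it reach the endpoint?** Section 8.4.2 says the profile is assessed by CTCAE. No section says that exempted bleeding is added to it.
6. **Is the information available?** Yes. Bleeding is asked about at visits 1, 2 and 3 and at the VAB 2/mastectomy visit. Section 12.1 has data abstracted from the family history records onto CRFs. At visit 4 the listed question is only whether menstruation has started.

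So the event is expected, asked about and written down. The protocol names no bleeding item, no grade and no place for it in the side effect profile.

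**The case against.** The strongest reply is that the exemption is narrower than it looks. Its subject is normal menstrual bleeding, with spotting as a sub-item, so spotting between periods on UA could still count as an adverse event under the general definition. That reading is open, and the text does not say that spotting can never be an adverse event. But it does not draw the line either, and two members of staff could classify the same event differently.

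A reader might also infer that spotting is held in the notes alone and can never reach the endpoint. The documents do not support that. Section 12.1 feeds the notes into CRFs, and Appendix 5 has a symptom review separate from adverse event documentation at weeks 5, 9, 12–13 and 17. Section 8.4.2 does not confine the profile to the adverse event log. What stands is that none of these streams specifies a bleeding item or a grade.

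It may be said that CRF content and table layout belong in documents not shown here; section 12.2 leaves CRF design to the team. That is fair for layout. The classification rule, however, is in the protocol, and it is the rule that conflicts with section 5.6.3.

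A reader might further fear for the section 10 comparison by development of amenorrhoea. That does not follow: bleeding is asked about on treatment whatever its adverse event status.

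**Conclusion.** The point holds as a conflict between sections with a probable, unquantified effect on a secondary endpoint. Followed as written, the CTCAE side effect profile would probably understate bleeding effects of UA. This rests on two assumptions: that staff take the exemption to cover spotting on treatment, and that the profile is compiled mainly from graded adverse events. Both are natural readings, but neither is stated outright.

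The size of the omission would be the share of treated women with spotting that goes unlogged, and the protocol gives no figure for that share. A reader might treat the gap as a reported zero among the 30 women and attach a confidence limit to it. That is not supported, because an exempt event type produces no row in the table, not an observed count of zero.

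The primary Ki67 endpoint is untouched. The change should still be made: it is cheap, and tolerability is part of the rationale.

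**What to change.** Reconcile sections 5.6.3, 8.4.2, 13 (adverse events that do not require reporting) and 13.1:

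- State whether on-treatment intermenstrual bleeding or spotting falls within normal menstrual bleeding.
- Keep it exempt from reporting to the sponsor.
- Record it as a structured CRF item at the visits where bleeding is already asked about: yes/no, dates, menstrual or intermenstrual, and CTCAE grade.
- Tabulate it with the side effect profile under section 8.4.2.

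The cost is one CRF item and one table row. No visit, treatment or stopping rule changes. For women already through the study, the item can be filled from the family history notes as far as those entries allow.

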### **Causality Assessments**

The process for causality assessments is described in **MFT's SOP Pharmacovigilance for Trust-Sponsored Clinical Trials of Investigational Medicinal Products (CTIMPs)**.

### **Expectedness Assessments**

The Chief Investigator on behalf of the Sponsor will assess each SAE to perform the assessment of expectedness.

The process for expectedness assessments is described in **MFT's SOP Pharmacovigilance for Trust-Sponsored Clinical Trials of Investigational Medicinal Products (CTIMPs)**.

The expectedness assessment should be made with reference to the current Reference Safety Information (RSI) for the IMP in this trial (Ulipristal Acetate SPC). Expectedness decisions must be based purely on the content of the RSI; other factors such as the participant population and participant history should not be taken into account. Expectedness is not related to what is an anticipated event within a particular disease.

SAEs which add significant information on specificity or severity of a known, already documented adverse event constitute unexpected events. For example, an event more specific or more severe than that described in the RSI is considered unexpected.

### 13.1 Recording and reporting of SAEs AND SUSARs

**MFT SOP Pharmacovigilance for Trust-Sponsored Clinical Trials of Investigational Medicinal Products (CTIMPs) must be used for safety reporting.**

AEs, ARs, SAEs, SARs and SUSARs must be recorded and reported as follows:

- For AEs / SAEs – from consent until the time of the last participant visit
- For ARs / SARs and SUSARs – from the 1st IMP dose until the time of the last participant visit

All AEs must be recorded in the participant's CRF in the AE log and in the patient's family history notes. SAEs/SARs/SUSARs must be recorded in the participant's CRF in the AE log and in the patient's family history medical records and must be reported to the Sponsor and other relevant departments/individuals **within 24 hours** of the research staff becoming aware of the event according to the instructions in **SOP Pharmacovigilance for Trust-Sponsored Clinical Trials of Investigational Medicinal Products (CTIMPs) must be used for safety reporting.**

(S)AEs and (S)ARs will be evaluated for duration and intensity according to National Cancer Institute Common Terminology Criteria for Adverse Events V4.0 (NCI-CTCAE) or MedDRA (Medical Dictionary for Regulatory Activities)

Investigator reports of suspected SARs will also be reported by the CI or their delegate to Gedeon Richter (manufacturer).

### 13.2 Responsibilities for safety reporting

Chief Investigator (CI), Co-investigators, Study doctors on the delegation log:

- Checking for AEs and ARs when participants attend for treatment / follow-up.
- Using medical judgement in assigning seriousness, causality and expectedness using the Reference Safety Information approved for the trial. The Principal Investigator, Co-investigators or Study doctor designated to carry out this function on the trial delegation log will assess each SAE to determine the causal relationship with the IMP, and will answer 'yes' or 'no' to the question "Do you consider that there is a reasonable possibility that the SAE may have been caused by the IMP?" A guide to the interpretation of the causality question is found in Appendix 1 of this clinical trial protocol.
- Ensuring that all SAEs and SARs (including SUSARs) are recorded and reported to the Sponsor within 24 hours of becoming aware of the event and provide further follow-up information as soon as available.
- Ensuring that AEs and ARs are recorded and reported to the Sponsor in line with the requirements of the protocol and *MFTSOP Pharmacovigilance for Trust-Sponsored Clinical Trials of Investigational Medicinal Products (CTIMPs)*.

Chief Investigator (CI) / delegate or independent clinical reviewer:

- Clinical oversight of the safety of patients participating in the trial, including an ongoing review of the risk / benefit.
- Using medical judgement in assigning seriousness, causality and expectedness of SAEs.. The Chief Investigator, Co-investigators or Study doctor designated to carry out this function on the trial delegation log will assess each SAE to determine the causal relationship with the IMP, and will answer 'yes' or 'no' to the question "Do you consider that there is a reasonable possibility that the SAE may have been caused by the IMP?" A guide to the interpretation of the causality question is found in Appendix 1 of this clinical trial protocol.
- Using the relevant safety information (RSI) in assigning expectedness. The Chief Investigator, on behalf of the Sponsor, will assess each SAE to perform the assessment of expectedness. ***If the CI is unavailable the Sponsor will find an alternative medically qualified individual with the appropriate knowledge to perform this task.***
- Immediate review of all SUSARs.
- Review of safety signal analysis and SAE trends in accordance with the MFT SOP Pharmacovigilance for Trust-Sponsored Clinical Trials of Investigational Medicinal Products (CTIMPs) and the Risk Management Plan for MFT Sponsored CTIMPs.
- Preparing the clinical sections and final sign off of the Development Safety Update Report (DSUR).

- Reporting safety information to the Sponsor oversight committees identified for the trial (Trial Management Group (TMG)) according to the Risk Management Plan for MFT Sponsored CTIMPs – *this function can be given to the Clinical Trials Manager/other suitable individual but the CI remains accountable to the Sponsor*).
- Inform Gedeon Richter (manufacturer) of any SUSARs.

Sponsor:

- Central data collection and verification of all reported SAEs, SARs and SUSARs onto a database.
- Expedited reporting of SUSARs to the Competent Authority (MHRA in UK) and REC within required timelines.
- Checking for (annually) and notifying PIs of updates to the Reference Safety Information for the trial.

Trial Management Group (TMG):

See section 16.1 below.

### **13.3 Out of hours contact arrangements**

When joining the study, the subject is given a Patient Information Sheet (PIS) which contains contact details of the study team and Chief Investigator during working hours.

Investigational Medicinal Product (IMP) packaging will include the switchboard number for the hospital and the name of the PI on the label.

If a trial patient is admitted via A&E at Wythenshawe Hospital, information regarding the trial will be found in the patient's hospital notes, including the PIS, which will state the CI responsible for the study.

At each study visit the research nurse will stress to the participant should they feel unwell outside of the hours 8am-4pm Monday to Friday they should go to their GP or A&E. When the participant is feeling well enough to do so they are asked to contact the research team to inform them of the details of the event.

### **13.4 The type and duration of the follow-up of subjects after adverse events.**

Adverse events will be followed up until the safety visit 4 weeks after the last dose of IMP.

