#### 5.6.4 ALT

If at any point when the ALT is measured it is found to be more than three times the upper limit of normal, UA must be permanently discontinued.

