## 6.2. Exclusion criteria:

- Personal history of breast, uterine, cervical or ovarian cancer
- Breast feeding within the last 3 months
- Pregnant or planning for pregnancy in the next 6 months. Pregnancy must be excluded with serum  $\beta$ hCG.
- Known hypersensitivity to radiological contrast media
- Known hypersensitivity to ulipristal acetate or any of its excipients (microcrystalline cellulose, mannitol, croscarmellose sodium, talc, magnesium stearate)
- Current treatment with:
  - Anti-estrogens (e.g. tamoxifen or raloxifene), GnRH analogue therapy (e.g. goserelin or buserelin) or hormonal contraceptives including androgens such as cyproterone acetate. Such treatments must have been stopped for at least 6 months and regular menstrual cycles resumed.
  - Oral corticosteroids at any dose, these must have been stopped for at least 1 month with low likelihood that retreatment will be required
  - Antiplatelet or anticoagulant therapy – must have been stopped for at least 7 days and clotting be at satisfactory levels (see below)
  - moderate or potent inhibitors of CYP3A4 (for list see appendix)
  - potent inducers of CYP3A4 (for full list see appendix 1)
- APTT and PT above the upper limit of the normal institutional ranges. Hb <100g/l and platelet count <150x10^9/l. bilirubin, ALT , ALP or LDH >1.5xULN.

- Previous/current diagnosis of hepatitis
- Diagnosis of cirrhosis of the liver
- Co-morbidity that would put the patient at increased risk such as recognised bleeding diathesis, moderate to severe hepatic impairment, moderate or severe renal impairment (eGFR <60 ml/min/1.73m^2), severe asthma not adequately controlled with corticosteroids (note steroid usage precludes trial entry)
- Prior breast enhancement/augmentation surgery
- Genital bleeding of unknown aetiology or for reasons other than uterine fibroids

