### 6.3 Withdrawal of Subjects

Participants have the right to withdraw from the study at any time for any reason. The investigator also has the right to withdraw patients from the study drug in the event of inter-current illness, AEs, SAE's, SUSAR's, protocol violations, administrative reasons or other reasons. It is understood by all concerned that an excessive rate of withdrawals can render the study un-interpretable; therefore, unnecessary withdrawal of patients should be avoided. Should a patient decide to withdraw from the study, all efforts will be made to report the reason for withdrawal as thoroughly as possible. Should a patient withdraw from study drug only, efforts will be made to continue to obtain follow-up data, with the permission of the patient.

The reason for withdrawal will be recorded in the CRF.

If the participant is withdrawn due to an adverse event, the investigator will arrange for follow-up visits or telephone calls until the adverse event has resolved or stabilised.

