**Visit 4 Day 113  $\pm$  4 days (week 17)**

During this visit the participant will:

- be asked if they are happy to continue in the trial
- have adverse events from the VAB visit and any other adverse events documented
- have any changes in their concomitant medications documented
- have their weight recorded
- have blood samples taken for LFT of which bilirubin, ALT, ALP, LDH will be measured
- be asked if they have started their menstrual period

Should a participant experience treatment emergent clinical symptoms or signs of liver disease whilst participating in the study they will be advised to contact the research team as soon as possible for assessment which will include repeat LFTs of which bilirubin, ALT, ALP and LDH will be recorded. Therefore, assessments of this nature could be conducted outside of the scheduled study visits.

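### Section 13.4 ends adverse-event follow-up at the 4-week safety visit whether or not the event has resolved, so for completers the protocol requires no follow-up of a non-serious open event or an asymptomatic abnormal LFT found at Visit 4

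*Protocol*

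**What the plan says.** Section 13.4, which sets the type and duration of follow-up after adverse events, consists of one sentence: "Adverse events will be followed up until the safety visit 4 weeks after the last dose of IMP".

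Section 6.3 applies a different standard to one group. For a participant "withdrawn due to an adverse event, the investigator will arrange for follow-up visits or telephone calls until the adverse event has resolved or stabilised". Section 13.4 does not mention this group.

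For completers the safety visit is Visit 4 (section 7.1, Day 113 ± 4). Two of its items matter here. Participants "have blood samples taken for LFT of which bilirubin, ALT, ALP, LDH will be measured", and they "have adverse events from the VAB visit and any other adverse events documented". No step is attached to an abnormal result or to an event that is still open. The same visit text allows unscheduled liver tests, triggered by "treatment emergent clinical symptoms or signs of liver disease".

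The one ALT rule, in section 5.6.4, is that if ALT is "more than three times the upper limit of normal, UA must be permanently discontinued". It is repeated at Visits 1, 2 and 3 but not at Visit 4.

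**The concern.** A fixed end date serves well for deciding which new events are collected. It serves less well for deciding when to stop looking after an event already found. Section 13.4 uses the same date for both purposes, and the final liver test is drawn at the very visit where follow-up ends. An abnormality first seen in that sample therefore has no follow-up period under the rule as written.

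What is at stake is participant protection, not inference. Section 11.1 says the women are unlikely to gain physically from taking part. Section 11.2 lists haematoma, bleeding and infection among the risks of biopsies done for the study. The exclusions for hepatitis and cirrhosis and the mandatory ALT stop show that liver safety is taken seriously during treatment. Section 16 convenes no independent data monitoring committee and gives regular safety review to the trial management group.

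**Working it through.** No figure in the plan needs reproducing. The check is a reading of every provision that could require follow-up of a completer after Visit 4, plus one day count.

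**Provisions set side by side**

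| Provision | What it requires | Does it reach a completer's non-serious open event or asymptomatic abnormal LFT after Visit 4? |
|---|---|---|
| 13.4 | Follow-up to the 4-week safety visit | No, it ends there |
| 6.3 | Follow-up until resolved or stable, for women withdrawn because of an adverse event | No, completers are not withdrawn |
| 5.6.4 and Visits 1–3 | Permanent stop of UA for ALT above 3×ULN | No, UA has already ended |
| 7.1, Visit 4, unscheduled LFTs | Assessment with repeat LFTs for clinical symptoms or signs of liver disease | Only if symptoms or signs appear |
| 7.1, telephone call after VAB 2 | Adverse events documented | No, it precedes Visit 4 |
| 13, definition of adverse events for the trial | Critical adverse events and laboratory abnormalities reported to the sponsor | Reporting only |
| 13.1 | All adverse events recorded in CRF and notes up to the last participant visit | Recording only |
| 13.2, investigators' reporting duties | Further follow-up information on SAEs and SARs | Serious events only |
| 13.2, Chief Investigator | General clinical oversight of participant safety | No repeat test or contact specified |

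None of these provisions requires a repeat test or further contact in the case described. Recording is required and, for a critical finding, reporting to the sponsor.

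**Relation between 13.4 and 6.3.** For a woman withdrawn because of an adverse event, 6.3 gives an open-ended duty and 13.4 a closed one. The two fit together if 6.3 is read as the specific rule and 13.4 as the general one, but the text does not say so. For a completer there is no such choice, because only 13.4 applies.

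**Day count for biopsy events**

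- Second biopsy or mastectomy: Day 78 to Day 85 (section 7.1).
- Visit 4: 113 − 4 = Day 109 to 113 + 4 = Day 117.
- Shortest interval: 109 − 85 = 24 days.
- Longest interval: 117 − 78 = 39 days.
- Nominal visit day after a Day 85 procedure: 113 − 85 = 28 days.

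A second-biopsy event is therefore asked about by telephone and again 24 to 39 days after the procedure. Only a non-serious event that lasts beyond Visit 4 is left without required follow-up.

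**Liver tests.** An ALT first raised at Visit 3 has one scheduled repeat, at Visit 4. One first raised at Visit 4 has none.

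**The case against.** The strongest reply is that a fixed window is a legitimate choice, that 6.3 is the specific rule for those who need more, and that the remaining gap is small. Much of this stands. The two sections can be reconciled, and the gap is confined to non-serious events and asymptomatic laboratory values in completers. It does not answer the point for completers, because no specific rule covers them.

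A second reply rests on duties elsewhere. Section 13.2 gives the Chief Investigator general clinical oversight, not limited to serious events. The section 13 definitions also let an important medical event be judged serious, which brings in the duty to supply follow-up information. A conscientious investigator would probably repeat a markedly raised ALT. Even so, these provisions permit follow-up without requiring it, and 13.4 says when it ends.

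A third reply is the sponsor's pharmacovigilance SOP. Section 13 opens by requiring staff to know it, and 13.2 ties adverse-event recording and reporting to it. It may govern events open at the last visit. It cannot be checked here, so the finding is limited to what the protocol requires. Section 13.4 does not name the SOP and sets its own duration.

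A reader might also draw stronger conclusions that the protocol does not support:

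- *Nothing is required at Visit 4.* Not so: recording is required, and reporting if the finding is critical.
- *Visit 4 is the one liver test of five whose action was forgotten.* The screening cut-off ("ALP or LDH >1.5xULN", with the same limit for bilirubin and ALT) is an eligibility rule, and at Visits 1–3 the rule ("If ALT is more than three times the upper limit of normal, UA must be permanently discontinued") stops the drug. Neither is a follow-up rule, and at Visit 4 a completer has no drug to stop.
- *The same ALT is followed to resolution at Visit 1 but not at Visit 4.* That holds only if stopping UA for ALT counts as withdrawal due to an adverse event. Neither 5.6.4 nor 6.3 says it does.

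**Conclusion.** The point holds in a limited form. As written, 13.4 lets follow-up of a completer end with an event unresolved. No provision in the protocol requires a repeat test or further contact for a non-serious event still open at Visit 4 or for an asymptomatic abnormal LFT first found there. Serious events, symptomatic liver disease and women withdrawn because of an adverse event have provisions of their own, although 13.4 does not expressly except the last group.

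The size in women cannot be given, because the protocol states no rate of events open at Visit 4. For second-biopsy events the gap begins 24 to 39 days after the procedure. The conclusion assumes that the unseen SOP does not impose its own follow-up on such events. A reader might infer harm to the trial's main result, but the primary Ki67 analysis uses tissue taken before Visit 4 and is not affected. This is a cheap improvement to participant safety.

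**What to change.** Amend section 13.4 to read, in substance: any adverse event, including a clinically significant abnormal LFT, that is unresolved or first found at the safety visit will be followed by visit or telephone, with repeat LFTs where relevant, until resolved or stabilised; this applies to completers as well as to women withdrawn under section 6.3. Add one line at Visit 4 in section 7.1 sending abnormal LFTs and open events to section 13.4.

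This uses the standard already adopted in 6.3 and removes the unstated relation between the two sections. The cost is two short text changes and, for the women concerned, a few extra calls or repeat blood tests in a 30-woman trial. Under section 4 the trial already stays open after Visit 4 until DNA results have been returned.
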